### Retention

Several strategies will be used in order to maximise retention in the study. Given that the trial will be conducted entirely online, face-to-face contact with a research assistant will be non-existent or minimal. It is therefore essential to maintain contact with men in other ways, including:

Regular emails to ‘touch base’ and remind participants about the study.Gift certificates to show appreciation for men taking the time to participate, at immediate post-use and at 3 and 6-month follow-up (up to a maximum of $120 per participant across the study duration: $30 at immediate post-use, $40 at 3 months and $50 at 6 months). Vouchers will be emailed to their nominated email address with an accompanying email thanking them for their participation.Use of friendly, warm communication strategies in all communication to enhance the feeling of support.

Similar strategies will be implemented for ensuring retention of partner participants, including:

Gift certificates to show appreciation for partners taking the time to participate, at 3 and 6-month follow-up (e.g., $30 at 3 months and $30 at 6 months).

### Intervention group (the BETTER MAN website)

BETTER MAN is a healthy relationship website for early intervention that offers a private, accessible and non-judgemental resource for men who may use IPV. It applies behaviour change principles to promote men’s readiness to change using the well validated Transtheoretical Model psychological theory on which motivational interviewing (MI) is based. MI is a person-centred, strengths-based technique to enhance motivation to change through challenging ambivalence to increase help-seeking [45]. Previous MI approaches to engage men prior to MBCPs have demonstrated significant increases in program attendance and completion [20, 46]. MI techniques [45] used throughout BETTER MAN encourage awareness and self-reflection, reduce stigma, and improve communication skills. They enable men, who will vary in their readiness to change, to weigh up their situation and options, to form action plans that meet their personal priorities, tailored to their self-perceived Stage of Change (pre-contemplation, contemplation, preparation, action and maintenance). With the ultimate aim of improving safety for partners and children, BETTER MAN involves the following MI techniques: Engage, Focus, Evoke, Plan (see Fig. 1).

The BETTER MAN website is composed of three sequential modules: Better Communication, Better Values, and Better Relationships, with all modules having online messaging tailored to user input. The Better Communication module explores how a man’s communication style may differ with a partner compared to others, and promotes positive communication (e.g., listening, staying calm). The module also contains a grounding breathing exercise and an activity for recognising signals of potentially abusive behaviour. The Better Values module explores how a man’s behaviour in relationships aligns with his self-identified values using hypothetical scenarios to highlight discrepancy between values and behaviour. The Better Relationships module encourages a man to reflect on the health of his relationship and his use of controlling behaviour and violence (physical, emotional, sexual abuse), and weigh up pros/cons of his relationship (including with his children if applicable). A final Action Plan section reinforces help seeking and provides resources for related areas (e.g., parenting, alcohol/drug use, mental health). The modules take about 30 min and men can go back to the website any time.

### Comparison group

Men in the comparison group will be directed to an alternate website representing the usual available resources and standard care for men seeking help online in Australia. This website will be specially built for the study based on content from HealthDirect, a government-funded service providing quality, approved information about a range of health topics. One of the website sections is about how to build and maintain healthy relationships with partners and family members. The section answers questions such as: What are the signs of a healthy relationship? What are the benefits of healthy relationships? Communication in a healthy relationship? How can I maintain healthy relationships? The website also provides a list of resources for support, a comprehensive directory of Australian websites that people can search for further related information and a 24-hour health advice hotline. The comparison website will be built in a way that reflects the contents in the HealthDirect section on healthy relationships.

### Ethics, safety and data monitoring

Ethics approval for this study was obtained from the Human Ethics Research Committee at the University of Melbourne (HREC 1,442,953).

#### Safety of participants and researchers

Information is provided to all participants (men and partners) regarding the safe use of computers and the internet. Additionally, BETTER MAN is designed with a ‘quick escape’ bar that allows immediate exit and log out from BETTER MAN and returns the user to a weather forecast website. All automated emails sent to participants have the subject header “Better Man Project” and come from a generic email address ([contact]). Should a participant contact a member of the research team because they are upset due to their participation in BETTER MAN, the researchers will refer to the study distress protocol in their response. The protocol includes exploring with the individual whether they have someone they can talk to who will understand and be supportive. The research team member will discuss with the participant where they might seek support, including from the agencies detailed on the resource list provided to all participants. In the unlikely event that a participant discloses child sexual abuse in their answer to the few open-ended questions in the surveys, researchers will follow State-based mandatory reporting requirements. Participants are able to withdraw from the trial at any time on request.

Regular team meetings will be held for researchers to debrief about the project and any incidents that have arisen. If researchers are distressed at any time from the work, they will be offered referrals for appropriate counselling.

#### Data storage, monitoring and dissemination

Deidentified datasets downloaded from REDCap will be stored on password-protected computers at The University of Melbourne, with access limited to research team members named on the ethics application. Deidentified data will be retained for a minimum of five years after study completion.

An independent Data Monitoring Committee (DMC) has been established to ensure that the trial is conducted appropriately and safely. The DMC will meet at least once a year, following data collection milestones or major trial events. The DMC is composed of diverse experts in randomised controlled trials and IPV. They will ensure that trial participants are protected and will monitor the overall conduct of the trial. To further enhance adherence to study processes, all staff members involved in the trial will have access to a detailed protocol document, as well as the approved ethics application.

The study findings will be disseminated through peer-reviewed publications, presentations at academic conferences and for the sector, and via social media and other online platforms. No identifying details will be used when reporting study findings.

### Outcomes

Outcomes, measures, and hypotheses for the BETTER MAN trial are shown in Table 2. Primary outcome is difference between the intervention and comparison groups in the percentage of men who report undertaking help-seeking behaviours for relationship issues in the last six months (as measured by men’s self-reported use of MensLine, Men’s Referral Service, MBCP, or other counselling services for relationships), 6 months post-intervention. The secondary outcomes are differences between the two study groups in:

mean number of behaviours in relationships identified as abusive as measured by the 7-item “Understanding of Violence against Women Scale” from *The National Community Attitudes towards Violence against Women Survey* [37], immediately after website use;mean score on readiness to change as measured by 10 items adapted from the *Contemplation Ladder* [47, 48], immediately after website use and 3 months post-baseline.cost-effectiveness at 6 months post-baseline.

Additional data will be collected as hypothesised mediators and moderators (see Table 3). Mediators of the outcomes include intention and confidence to seek help (rating scale 1–10), alcohol use, depression symptom severity and use of the website (accessed, time spent, pages visited in 6 months). Moderators of the outcomes include baseline levels of mental health (depressive, anxiety and PTSD symptoms) and type of IPV perpetrated.

### Sample size

Based on the response rate (108/137, 79%) from the BETTER MAN pilot [31] and allowing for attrition rate of 30% at six months (based on previous studies [39]), 266 men at baseline (133 per group) will provide 80% power (alpha 5%, 2-sided test) to detect a meaningful difference of 20% (based on our pilot work [31]) in the percentage of men who initiate help-seeking for relationship issues between intervention (50%) and comparison (30%) groups. Additionally, based on the pilot, we expect up to 15% of partners will be recruited.

### Data analysis

#### Statistical methods for primary and secondary outcomes

Participants’ characteristics will be summarised using means and standard deviations (or percentiles as appropriate) for continuous data, and frequencies and percentages for categorical data, for both study groups. Primary analysis will use an intention to treat approach [49], where all individuals will be included in the analysis according to the study group they were assigned, whether they completed all, part or none of the intended intervention.

Logistic regression will be used to estimate the odds ratio of men’s help seeking activities at 6 months for the intervention against the comparison group. Generalised linear model with the identity link function and binomial family will be used to estimate the absolute difference in the percentage of men’s help seeking activities between the two study groups. Both models will adjust for whether the participant had children or did not have children and self-reported help-seeking behaviours measured at baseline. The estimated intervention effect for the primary outcome will be presented as both an odds ratio comparing the intervention to the comparison group (relative effect) and between-group difference in the percentages (absolute effect) with their respective 95% confidence intervals (CI), and the p-values estimated using logistic regression.

Mixed effects linear regression models will be used to estimate the between group difference in the mean scores for the secondary continuous outcomes, namely, awareness of behaviours as abusive immediately after the use of the website completion, and readiness to change at two assessment time points, after the use of the website completion and 3 months post-baseline. Study group and time of measurement and whether the participants had children will be included as fixed effect and random intercept terms for individuals (to account for repeated measurement). A two-way interaction between the study group and time will be fitted to estimate the between-group difference in mean outcome at each measurement time point, but we will constrain the baseline means between the study groups to be equal. The estimates will be presented as difference in the mean outcome between the intervention and comparison groups at immediate post-intervention and 3 months (as appropriate), with 95% confidence intervals and p-values.

Handling of missing data will be detailed in a statistical analysis plan (SAP) informed by a blinded review of data. The SAP will also elaborate on additional analyses such as sensitivity analyses, analysis to assess non-adherence to the intervention on the estimated intervention effects and mediator/moderator analyses. The SAP will be made available prior to the statistical analysis of the primary outcome.

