### Trial design

The BETTER MAN trial is a two parallel group, pragmatic, randomised controlled superiority trial to test an online healthy relationship tool for men in the Australian community who may use IPV and its effectiveness in increasing men’s help seeking behaviours for relationship issues. Individuals will be randomly allocated 1:1 to the intervention or comparison websites. The protocol is described in accordance with the SPIRIT statement [32].

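### The adjusted identity-link model for the absolute difference does not in general fit with the logistic model that supplies the p-value; standardising from the logistic model would be safer

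*Protocol article*

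**What the plan says.** The Outcomes section sets the primary outcome on the absolute scale: "Primary outcome is difference between the intervention and comparison groups in the percentage of men who report undertaking help-seeking behaviours". The Sample size section powers the trial on that scale, "between intervention (50%) and comparison (30%) groups", and the economic evaluation reports cost per additional man seeking help, so the same difference is needed there.

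Under Statistical methods for primary and secondary outcomes, two models share the primary analysis. Logistic regression gives the odds ratio. For the difference: "Generalised linear model with the identity link function and binomial family will be used to estimate the absolute difference in the percentage". Both models adjust for having children and for "self-reported help-seeking behaviours measured at baseline", and no treatment-by-covariate interaction is stated for either. The odds ratio and the difference are to be reported "with their respective 95% confidence intervals (CI), and the p-values estimated using logistic regression". The difference and its interval therefore come from one model and the p-value from another.

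**The concern.** The logistic model assumes one common odds ratio across the baseline strata. The identity-link model assumes one common risk difference. When baseline help-seeking predicts the outcome and the intervention works, a common odds ratio generally means that the risk difference varies between prior help-seekers and other men. One primary result would then rest on two assumptions that do not fit together.

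Three consequences follow:
- The interval for the difference and the reported p-value can fall on opposite sides of 5%.
- The identity-link coefficient averages the stratum differences with weights that favour strata whose risks are near 0 or 1, so it need not equal the difference in percentages that the trial is about.
- If prior help-seekers are close to 100% at six months, a common additive effect pushes fitted risks against 1 and the model may not converge.

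The covariate is the baseline version of the outcome, so strong prognosis is plausible, but the protocol gives no figures for it.

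**Working it through.** **Inputs from the protocol.** 30% v 50%; "266 men at baseline (133 per group) will provide 80% power (alpha 5%, 2-sided test"); "allowing for attrition rate of 30% at six months"; 1:1 allocation.

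**Reproducing the sample size.** With pooled variance, two-sided 5% and 80% power, n per group = [1.960·√(2·0.4·0.6) + 0.842·√(0.3·0.7 + 0.5·0.5)]² / 0.20² = (1.358 + 0.571)² / 0.04 ≈ 93. Dividing by 0.70 gives 132.9, so 133 per group and 266 in all. This matches. The checks below use 93 analysed men per group.

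**Assumed inputs.** The share of men already seeking help at baseline (20% unless stated) and the six-month rates by baseline help-seeking are not in the protocol. They were varied while the overall rates were held near 30% and 50%.

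**Step 1: the two models conflict.** Take other men going from 17.5% to 39.4% and prior help-seekers from 80% to 92.5%, an odds ratio of about 3.1 in both strata. The differences are 21.9 and 12.5 points. The overall difference is 0.8·21.9 + 0.2·12.5 = 20.0 points. The logistic model fits this exactly; a common risk difference does not. The exception is when the strata are mirror images about 50%. For example, 22.5% to 42.7% and 57.3% to 77.5% share both an odds ratio of 2.57 and a difference of 20.2 points. That is why moderate rates do little harm.

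**Step 2: what the identity-link coefficient estimates.** In large samples (baseline help-seeking as the only covariate) it is the average of the stratum differences with weights proportional to stratum share ÷ [m₀(1−m₀) + m₁(1−m₁)], where m₀ and m₁ are the stratum's fitted risks.
- Prior help-seekers 90% in both arms, others 15% to 40%: true overall difference 0.8·25 + 0.2·0 = 20.0. The limit is 17.9, which implies a weight of 17.88/25 = 0.715 on the others instead of 0.80.
- The Step 1 example: limit 19.2.
- Prior help-seekers 60% to 79.4%, others 22.5% to 42.7%: limit 20.0 for a true 20.0.
- 30% prior help-seekers, at 80% in both arms, others 8.6% to 37.1%: limit 20.3 for a true 19.95. The direction is therefore not fixed.

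**Step 3: simulation with 93 per group, true difference 20 points.** Ranges are from separate runs of 1,500 and 2,000 trials.

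| Prior help-seekers at 6 months | Non-convergence | Mean estimate | CI/p disagreement |
|---|---|---|---|
| 45% to 65% | 0% | 20.1 | 1.7% |
| 50% to 65% | 0.2% | 20.1 | 1.7% |
| 60% in both arms | 0.1% | 20.3 | 1.6% |
| 80% in both arms | 7–10% | 19.1 | not tabulated |
| 70% to 90% | 17–27% | not tabulated | not tabulated |
| 90% in both arms | 39–44% | 17.4 | 7% |

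A further run gave 0.1–0.2% non-convergence, no bias and 2–3% disagreement at 50–65%. At 70–90% it gave 5–29% non-convergence, estimates of 17.7–19.7 and 3–7% disagreement.

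Non-convergence depends on the fitting algorithm and on what counts as failure. When fitted risks outside 0–1 also counted, 90% in both arms gave 60%, and 90% to 96.9% gave 80–88%. These are orders of magnitude, not forecasts.

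**Step 4: the alternative.** The risk difference standardised from the adjusted logistic model averaged 19.8–20.3 in every 20-point scenario. Its interval disagreed with the logistic p-value in about 1% of trials (0.2–1.2% across runs). Between 0% and 9% of trials were set aside for near-separation in the logistic fit.

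**The case against.** The strongest reply is that the size rests on rates that the protocol does not contain. The trial recruits beyond men already using support services, so 90% persistence among prior help-seekers is not a natural default. At 45–65% the identity-link model is almost harmless. Even at 90% in both arms, its interval covered the true 20 points in 92% of converged trials. A shift of 2–3 points is also small against the uncertainty: the unadjusted 95% half-width is 1.96·√(0.46/93) = 13.8 points. An adjusted identity-link binomial model is a recognised way to estimate a risk difference, and reporting relative and absolute effects from separate models is not in itself a contradiction. All of this stands, and it limits the point to an improvement worth making.

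Two stronger readings also fail. A reader might infer that the primary test is ambiguous. It is not: the protocol names logistic regression as the only source of the p-value, and the odds-ratio interval comes from that same model. A reader might also fault the absence of a plan for non-convergence. That belongs in the statistical analysis plan, which is promised before the primary analysis and is not shown here.

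What the reply does not remove is the mismatch itself. The protocol fixes both models, and a convergence fallback would not align the interval with the p-value.

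**Conclusion.** The point holds as a modest, conditional weakness in a stated method. If baseline help-seeking is prognostic and there is an effect, the two planned models are in general incompatible. The interval for the headline difference can then disagree with the p-value, and the coefficient is not in general the overall difference in percentages.

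On the assumed rates:
- **Prior help-seekers at about 50–65%:** about 0% non-convergence, negligible bias, about 2–3% disagreement.
- **70–90% in both arms, or rising to 90%:** about 5–40% non-convergence, about 3–7% disagreement, and an estimate lower by up to about 2–3 points near the ceiling.

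It would be wrong to conclude that the estimator is biased towards zero in general. The shift is under 0.1 point in moderate scenarios, and in one stronger scenario it went slightly upwards. Nor can the wording about men who initiate help-seeking be taken to show that the effect is confined to men not yet seeking help; the outcome counts any listed contact in the last six months. The hypothesis test and the 266 men are unaffected.

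**What to change.** Replace the identity-link model with marginal standardisation from the adjusted logistic model already planned. Predict each analysed man's risk under both allocations, average over all analysed men, and report the difference with a delta-method or robust 95% confidence interval (`margins` in Stata, the software the protocol names). Keep the odds ratio and p-value from the same fit. Covariates, sample size and test stay as they are. The change can be made in the statistical analysis plan before the primary analysis.

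The cost is one sentence and one post-estimation command. Two limits remain. About 1% of trials would still show disagreement between interval and p-value, because the two are computed on different scales. The logistic fit can also approach separation if nearly all prior help-seekers report contact at six months.

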### Economic evaluation

For the economic evaluation, resource use data from website software and men’s self-report will be valued at standard unit cost rates to estimate intervention delivery costs and impact of the intervention on costs of access/use and service use over the six months from the perspective of (i) government and (ii) men. The six-month time duration avoids the need for discounting. Economic evaluation will, as a first step, present a cost-consequences analysis with costs presented separately for government and men compared with the difference in all outcome measures. Cost-effectiveness will then be presented on the primary outcome, in terms of the additional cost per additional man reporting help seeking at 6 months.

Statistical analyses will be conducted in Stata Statistical software 17 [50].

#### Process evaluation

Process evaluation will focus on men’s experiences of behaviour change over time and the potential role of the BETTER MAN website in this process. We will use Interpretative Phenomenological Analysis methods [51] to explore the meanings men attach to behaviour change and how these meanings change over time. We will also examine what supports or services have been helpful and what factors may impede or facilitate change processes. We will also ask men to reflect on what elements of the BETTER MAN website may have been useful to them and why.

Semi-structured, in-depth interviews will be conducted via telephone with a sub-sample of up to 30 men and their partners (we estimate up to 10 partners may be recruited based on our pilot work) immediately after completion of BETTER MAN, and at 3 and 6-months post-use. We will recruit by asking men who complete the post-use survey if they are interested in taking part in an interview. Where possible, we will aim for diversity in terms of demographic factors (e.g., cultural background, location, sexual orientation). All interviews will be recorded and transcribed verbatim. Our analysis will take a trajectory approach [52], which aims to examine the experiences of the same group of participants over time. Analysis will first focus on the individual level, before examining patterns of change across the cohort.

